## Abstract

**Introduction:**

Millions of children in India still suffer from poor health and under-nutrition, despite substantial improvement over decades of public health programmes. The Anganwadi centres under the Integrated Child Development Scheme (ICDS) provide a range of health and nutrition services to pregnant women, children <6 years and their mothers. However, major gaps exist in ICDS service delivery. The government is currently strengthening ICDS through an mHealth intervention called Common Application Software (ICDS-CAS) installed on smart phones, with accompanying multilevel data dashboards. This system is intended to be a job aid for frontline workers, supervisors and managers, aims to ensure better service delivery and supervision, and enable real-time monitoring and data-based decision-making. However, there is little to no evidence on the effectiveness of such large-scale mHealth interventions integrated with public health programmes in resource-constrained settings on the service delivery and subsequent health and nutrition outcomes.

**Methods and analysis:**

This study uses a village-matched controlled design with repeated cross-sectional surveys to evaluate whether ICDS-CAS can enable more timely and appropriate services to pregnant women, children <12 months and their mothers, compared with the standard ICDS programme. The study will recruit approximately 1500 Anganwadi workers and 6000+ mother-child dyads from 400+ matched-pair villages in Bihar and Madhya Pradesh. The primary outcomes are the proportion of beneficiaries receiving (a) adequate number of home visits and (b) appropriate level of counselling by the Anganwadi workers. Secondary outcomes are related to improvements in other ICDS services, and knowledge and practices of the Anganwadi workers and beneficiaries.

**Ethics and dissemination:**

Ethical oversight is provided by the Committee for the Protection of Human Subjects at the University of California at Berkeley, and the Suraksha Independent Ethics Committee in India. The results will be published in peer-reviewed journals and analysis data will be made public.

**Trial registration number:**

ISRCTN83902145

Strengths and limitations of this studyThe study can provide important evidence on whether and the extent to which a large-scale mHealth intervention can improve maternal and child health and nutrition service delivery by the world’s largest child development programme in India.Application of the gold-standard cluster-randomised controlled trial design was not possible because of pre-determined programme assignment and rapid roll-out of the programme. Therefore, to find attributable impacts, this evaluation settles for a scientifically less robust but practicable quasi-experimental design consisting of matched control-villages and repeated cross-sectional measurements.Measurement biases may exist because blinding is not possible and primary outcomes are measured subjectively via interview-based recall or observations.Higher order impacts may be underestimated as the follow-up period of <12 months may be too short for the intervention to stabilise.

## Introduction

### Background and problem context

Millions of children in India continue to suffer from poor health and under-nutrition, despite decades of government programmes aimed at reducing this burden and some impressive gains through these years. In 2015–2016, 36% of children under 5 years of age were underweight, 38% were stunted and 21% were wasted as per the National Family Health Survey (NFHS-4), and these numbers represent only modest improvements over the past decade. Micronutrient deficiencies are widespread, with more than 58% of preschool children suffering from iron deficiency anaemia. Infant and neonatal mortality rates also remain high at 41 and 30 per 1000 live births respectively, despite substantive reductions over past decades^1^

The Integrated Child Development Services Scheme (ICDS), launched in 1975, is one of India’s national flagship programmes to support the health, nutrition, and development needs of children below 6 years of age and pregnant and lactating women, through a network of Anganwadi Centres (AWCs), each typically serving a population of 800–1000.^2 3^ Early observational studies found that ICDS is associated with better coverage and delivery of services related to nutrition, healthcare, and pre-school education and improved maternal and child nutrition.^4–6^ Using the NFHS data from 2005 to 2006, Kandpal^7^ and Jain^8^ found that ICDS is associated with small to modest improvements in child health and nutrition, especially among the most vulnerable populations.

However, several reviews and evaluations of ICDS over the past 18 years have also found persistent gaps, including inadequate infrastructure at the AWC, Anganwadi worker (AWW) service delivery issues (eg, poor quality supplementary food, few home visits and no counselling etc), human resource issues (eg, vacancies, increasing range of duties expected of the AWWs, inadequate training of AWWs, limited supervision etc) and poor data management (eg, irregularities in record keeping at AWCs, ineffective monitoring of service delivery etc).^3 4 9–11^ The most recent NFHS (2015–206) also highlights the gaps in ICDS service delivery. Only about 59% of children under 6 years received any service from an AWC, 53% received supplementary food services and 47% were weighed. Similarly, only 60% of mothers received any AWC services during pregnancy, and 54% received any service during the breastfeeding phase.^1^

With a goal to improve the functioning of ICDS, the Government of India launched the ICDS Systems Strengthening and Nutrition Improvement Programme (ISSNIP) in 2012 which focused on infrastructure upgradation and training of AWWs to build their knowledge on health and nutrition topics under the Incremental Learning Approach. At the same time, a pilot-scale mHealth intervention to improve ICDS service delivery was implemented in Bihar between 2012 and 2013. A randomised controlled trial of this intervention found a significant increase in the proportion of beneficiaries receiving visits from frontline workers at different life-stages - last trimester of pregnancy (42% vs 52%), first week after delivery (60% vs 73%) and complementary feeding stage >5 months after delivery (36% vs 45%).^12^ The intervention also significantly increased the proportion of beneficiaries receiving at least three antenatal care visits (29% vs 50%), the proportion of beneficiaries consuming at least 90 iron folic acid tablets during pregnancy (11% vs 17%), the proportion of mothers breastfeeding immediately after birth (62% vs 76%) and the proportion of mothers starting complementary feeding at the right time (32% vs 41%). Subsequently, the ISSNIP was restructured in 2015 by integrating ICDS in seven states with an at-scale mHealth intervention called Common Application Software (ICDS-CAS) installed on smart phones and with accompanying multilevel data dashboards. This system is intended to be a job aid for frontline workers, supervisors and managers, and aims to ensure better service delivery and supervision by enabling real-time monitoring and data-based decision-making.

While there is a growing body of evidence on the effectiveness of mHealth interventions, it almost entirely consists of small-scale studies or pilot interventions under well controlled settings, and often of poor research quality. For example, a systematic review examining 17 studies set in low and middle-income countries found that small scale mHealth interventions, particularly those delivered using SMS, were associated with increased utilisation of healthcare, including uptake of recommended prenatal and postnatal care consultation, skilled birth attendance and vaccination, but only two of these studies were graded as being at *low risk of bias*.^13^ Barnett and Gallegos^14^ reviewed nine studies that assessed the impact of using of mobile phones for health and nutrition surveillance, and found that while the available evidence suggests that mobile phones may play an important role in nutrition surveillance by reducing the time required to collect data and by enhancing data quality, the available evidence is of poor methodological quality and is generally based on small pilot studies and mainly focuses on feasibility issues. Another recent systematic review of 25 studies found evidence that mobile tools helped community health workers improve the quality of care provided, the efficiency of services and the capacity for programme monitoring.^15^ However, most of these studies were pilots and provided little or no information about the effectiveness of mHealth interventions when integrated with large-scale public health programmes.

This study seeks to address this critical gap in the evidence base in the context of the largest public health and nutrition programme in the world, ICDS, with 1.4 million AWCs serving at the grassroots level across India. The impact evaluation is conducted in two large states in India — Madhya Pradesh (MP) and Bihar — using a quasi-experimental, matched-controlled pre-measurement and post-measurement design. The overall evaluation framework consists of additional components such a process evaluation, a technology evaluation and an economic evaluation.

This evaluation is also timely as India launched the National Nutrition Mission on 8 March 2018 with the goal of reducing malnutrition in a phased manner across entire of India and subsumed ISSNIP and ICDS-CAS under it.^16^ Therefore, ISSNIP and ICDS-CAS are poised to be scaled-up rapidly to reach almost the entire population of India through 1.4 million AWCs by 2020. This scale-up effort will be informed by robust evidence on the effectiveness of the mHealth intervention, as well as on how its implementation can be improved.

### The ICDS-CAS intervention

Currently, the ICDS-CAS intervention is being implemented at scale in seven states, covering over 107 000 AWCs, and through them, a population of 9.8 million registered beneficiaries. The intervention consists of two components as follows.^17^

(1) An android CAS application and smartphones for AWWs and the female supervisor: The CAS app was developed on an open source mobile platform (CommCare). The app digitises and automates ten of the eleven ICDS paper registers maintained by AWWs, enables name-based tracking of beneficiaries, prioritises home visits at critical life-stages through a home visit-scheduler, improves record keeping and retrieval of growth and nutrition status of children, helps track immunisation, monitors the timeliness and quality of different services delivered by AWWs, and includes checklists and videos as job aids. A female supervisor typically manages a cluster of 10–20 AWCs and the CAS app is expected to help her monitor AWWs remotely, assess quality of service delivery, and serves as a job aid to train AWWs. The app is installed on new smartphones that are provided to the AWWs and supervisors. Both AWWs and supervisors are trained on the use of the app and how the features help them improve service delivery. Helpdesks at block and district levels for technical support are also established.

The CAS app is especially expected to improve home visit service delivery by AWWs through improved channels of information (easy access to past records of the beneficiary for customised messaging, educational animation videos as a job aid, life-stage-appropriate checklists for counselling messages) and timely nudges (automatic creation of visit-due lists, alerts for approaching or missed visits and timely intimation of delays to the female supervisor). Thus, improved home visits in terms of timeliness, frequency, and perhaps, a more effective message delivery mechanism are expected to result in increased knowledge and better recall of correct health and nutrition practices by the beneficiaries and higher demand for related government services. However, for the actual behaviours to change and sustain, supply side constraints must be addressed to meet the demand for services (eg, adequate supply of supplementary food, adequate provisions of Iron Folic Acid (IFA) tablets, regular immunisation camps, etc). Such improvements can be expected only in the mid-to-long-term because they are beyond the sphere of influence of ICDS-CAS and need more ICDS-wide improvements.

(2) A web-enabled dashboard for real-time monitoring by ICDS officials: Data generated at the AWC-level are aggregated and analysed via web-enabled dashboards for Child Development Project Officers at the project-level (typically an administrative block with 80–100 AWCs), District Programme Officers, the state ICDS Directorate and the Ministry of Women and Child Development (MWCD) at the national level. For example, the monthly progress reports are prepared manually at the AWC-level and then aggregated to the project-level which require weeks to be finalised and reviewed, but the CAS app and dashboards will automate and produce these reports in almost real-time. The dashboard infographics are expected to help identify bottlenecks at various levels more efficiently, help prioritise local issues, and allow managers to take data-driven decisions.

Figure 1 presents the ICDS-CAS information flow from the AWC through to the MWCD. The logic model in figure 2 summarises how ICDS-CAS is expected to improve service delivery, and ultimately improve health and nutritional outcomes in mothers and their children. The listed short-term outcomes are those expected to be achieved in the planned evaluation follow-up period of <12 months. The longer-term outcomes related to improved health and nutrition will be measured (except improvements in cognitive abilities) and analysed from a learning perspective, but these remain aspirational in the context of this evaluation study.

**Figure 1 F1:**
[figure not shown]
ICDS-CAS information flow from the Anganwadi Centre to the Ministry of Women and Child Development. Solid lines correspond to interactions. Dotted lines correspond to data flow. AWW, Anganwadi worker; CDPO, Child Development Project Officer; ICDS-CAS, Integrated Child Development Services-Common Application Software; MWCD, Ministry of Women and Child Development.

**Figure 2 F2:**
[figure not shown]
Logic model of ICDS-CAS and measurement of outcomes. AWW, Anganwadi worker; CDPO, Child Development Project Officer; DPO, District Programme Officer; ICDS-CAS, Integrated Child Development Services -Common Application Software; LS, lady supervisor; MWCD, Ministry of Women and Child Development.

#### Evaluation framework and research objectives

The ICDS-CAS evaluation framework consists of four components – an impact evaluation, a process evaluation, an economic evaluation and a technology evaluation. This paper describes the protocol for the impact evaluation in detail to guide the final analysis plan. The other three components are summarised online in supplementary figure 1 without binding details because their objectives, scope and methods can change as per the evolving learning needs of policy makers. We intend to analyse and publish impact evaluation and process evaluation as standalone research articles in peer-reviewed journals. The analysis and publication plan for the other components is yet to be determined.

10.1136/bmjopen-2018-025774.supp1Supplementary data

Corresponding to the short-term strategic objective of ICDS-CAS to improve quality and quantity of AWW and beneficiary interactions, the main research questions that impact evaluation seeks to answer are:Does ICDS-CAS improve the timeliness or frequency of home visits by AWWs for pregnant women, infants and their mothers?Does ICDS-CAS improve the extent or level of counselling by AWWs to pregnant women and mothers of infants?

## Methods and analysis

### Study setting

The ICDS-CAS programme is being implemented in 57 districts from seven ISSNIP states in India where the burden of under-nutrition is highest. This evaluation is restricted to two states, MP and Bihar, which were selected because of the possibility of selecting an ISSNIP district as a control, willingness of the states to support the evaluation, and the suggestions by the MWCD and the funding agency. Online supplementary table 1 presents key health and nutrition related indicators for villages in MP and Bihar. Both states have a high burden of under-five mortality (69 per 1000 live births in MP and 60 in Bihar), stunting (43.6% of children aged 0–5 years in MP, and 49.3% in Bihar) and anaemia (>55% of children and pregnant women in both states). Antenatal and delivery-related indicators are, in general, worse in Bihar, whereas MP has relatively poor demographic, water-sanitation, education and mortality related indicators– 8.3% of mothers in MP and 3% in Bihar had full antenatal care; 79.5% of households in MP and 98.2% in Bihar had an improved drinking-water source; and 50.2% of children aged 12–23 months in MP and 61.9% in Bihar were fully immunised.

10.1136/bmjopen-2018-025774.supp2Supplementary data

### Overview of the identification strategy

The attributable effects of ICDS-CAS will be identified using a quasi-experimental matched, controlled design with repeated cross-sectional pre-intervention and post-intervention measurements. This identification strategy is grounded in the Neyman–Rubin potential outcomes model where a matched cohort design can yield unbiased estimates of the causal effects under a strong assumption that all confounders are measured and balanced between the intervention and comparison groups.^18–20^ We use a 1:1 nearest neighbour propensity score matching (PSM) method to identify pairs of intervention and comparison villages.^21–25^ We plan to identify the effects of ICDS-CAS by comparing post-intervention outcome indicators between the matched groups, while controlling for any pre-intervention or baseline differences in the outcomes averaged at the village level and adjusting for the matched paired design.

### Sample design and power calculations

The initial sample size was determined as 400 villages in each arm with one AWW and, on average, three mother-child dyads in each village to measure a relative effect of 15% in a standardised counterfactual outcome [Normal(0,1)], with a significance level of 0.05, power of 80% and intra-cluster correlation (ICC) of 0.15. The actual baseline survey sample consisted of 852 villages to account for refusals and loss to follow-up.

After the baseline survey was conducted in June-August 2017, completely separate from our efforts to design the evaluation, the Indian government decided to include ICDS-CAS in the National Nutrition Mission. Consequently, the original evaluation objectives were revised to estimate the effects of ICDS-CAS separately for MP and Bihar to draw deeper insights into the heterogeneity of impacts. Therefore, the evaluation sample needed to be powered to detect smaller magnitudes of effects on a few process-related secondary outcomes. We plan to increase the sample power by following the same panel of villages but recruiting almost twice as many participants in each village – up to two AWWs and up to eight mother-child dyads. Assuming 200 pairs of villages and 1200 mothers per arm in each state, the sample will have 80% power at a significance level of 0.05 to detect an absolute difference of 5%–9%-points from the counterfactual levels between 10%–50% with ICC between 0.15–0.30. With 400 AWWs per arm in each state, the sample will have 80% power to detect effects of 8–12%-points for AWW level outcomes from the counterfactual levels of 10%–40% with ICC between 0.25–0.45.

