**Figure 3 F3:**
[figure not shown]
Sampling of study participants from Madhya Pradesh and Bihar. AWC, Anganwadi Centre; AWW, Anganwadi worker; CAS, Common Application Software; ICDS, Integrated Child Development Services; ISSNIP, ICDS Systems Strengthening and Nutrition Improvement Programme. Sources: # Women and Child Development Department, Government of Madhya Pradesh (MIS) http://mpwcdmis.gov.in/ (See1m5bxnuzmixun00bsctvfj))/DataEntryAwc.aspx (Accessed 8 June 2018); & Integrated Child Development Services, Government of Bihar http://www.icdsbih.gov.in/AnganwadiCenters.aspx?GL=16 (Accessed 8 June 2018); *Programme documentation from implementing agencies.

*Sampling of Intervention and Comparison Districts*: We randomly sampled three pairs of geographically and administratively matched intervention and comparison districts which shared a boundary and belonged to the same ICDS division to control for division-level confounders related to ICDS administration and management as well as cultural, social, environmental and economic factors at the micro-region scale. Within each state, we first sample three intervention districts. The corresponding control districts were selected by default if only one eligible district was available within the division, or randomly, if multiple comparison districts were available. In MP, the sample purposively included one pair of *tribal-only* districts from an equity-focused evaluation perspective. Figure 4 depicts the states and districts included in the evaluation.

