### Analysis plan

The effects of the ICDS-CAS intervention will be estimated as,

$$Y_{ij,\;t=1}=\;\beta_{0}+\;\beta_{1}\;.\;T_{j}+Pair\;ID_{K}+{\overset{-}{Y}}_{j,t=0}\;+\;\varepsilon ,$$

where

$Y_{ij,\;t=1}$ = an outcome of interest for beneficiary *i* in village *j* at endline (*t*=1);

$T_{j}$ = indicator variable which is 1 for intervention and 0 for comparison villages;

$Pair\;ID_{K}$ = fixed effects to account for *k* pairs of matched villages;

${\overset{-}{Y}}_{j,t=0}$ = average pre-intervention or baseline (t = 0) level of the outcome Y in the village;

*ε* = the error term of the model; and

*β*
_1_ = the effect of the intervention on outcome Y.

We will adjust for the pre-intervention average level of outcome in a village (${\overset{-}{Y}}_{j,t=0}$) to control for, *at least*, the measured or unmeasured *time invariant* village-level and higher-level confounders. To the extent that the endline questionnaires or sampling are different from those in the baseline, the construction of the outcome indicators in the baseline and endline may differ slightly, but such differences (if any) will not affect the interpretation of impact parameters estimated using the above model specification. Additionally, as a consistency check, we will estimate adjusted treatment effects that control for any observed imbalance in important baseline covariates. We may additionally control for covariates that can help increase the precision of impact estimates. We do not plan to correct the p-values for multiple comparisons because we only test a limited number of indicators for primary outcomes. However, for secondary outcomes, when multiple indicators related to a topic or theme are compared, we will adjust the p-values for multiple comparisons. We also plan to estimate the effects by adjusting for pairing only at the district level and not at the village-level if accounting for village matching results in substantial sample loss. All analyses will be done in STATA and replicated by two different analysts.

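### The per-state 80% power counts villages as the only clusters, so it holds only if matched districts show no residual difference within pairs after baseline adjustment

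*Protocol article*

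**What the plan says.** All references are to the protocol article.

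- **Sample design and power calculations.** After baseline, the objectives were revised to estimate effects separately for Madhya Pradesh and Bihar. The power statement reads: "Assuming 200 pairs of villages and 1200 mothers per arm in each state, the sample will have 80% power", and the claim for mothers is an "absolute difference of 5%–9%-points from the counterfactual levels between 10%–50% with ICC between 0.15–0.30". For AWWs, 400 per arm in each state are said to give 80% power for 8 to 12 points from levels of 10% to 40%, with ICC 0.25 to 0.45. The number of districts does not enter.
- **Study setting; Discussion.** The programme runs in 57 districts, and it is later to reach the control districts.
- **Sampling and recruitment of study participants.** "Within each state, we first sample three intervention districts"; each is paired with a neighbouring comparison district in the same ICDS division. Control villages are drawn from the paired comparison district.
- **Strengths and limitations.** Randomisation was ruled out "because of pre-determined programme assignment and rapid roll-out of the programme".
- **Analysis plan.** The model has "fixed effects to account for" the matched village pairs, plus the village mean of the outcome at baseline. It has no term for district within pair. Pairing at district level alone is a fallback if village matching loses too much sample.

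**The concern.** Within every village pair, arm and district coincide. Anything that moves one district of a pair and not the other, such as district management, a supply interruption or a parallel campaign, lines up exactly with the treatment indicator. Pair effects remove what the two districts share, but not the difference between them.

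A state-specific result is therefore a contrast of three districts with three. If districts within a pair differ at all beyond what baseline adjustment removes, the detectable differences are larger than stated, and a village-level test rejects a true null more than 5% of the time. Recruiting more mothers per village, the step taken to gain power for the state-specific objective, does not reduce this component. The results are meant to inform national scale-up, so the condition should be visible to readers.

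**Working it through.** **1. Reproducing the stated figures.** Inputs from the power section: 200 villages and 1200 mothers per arm per state (6 per village), 80% power, alpha 0.05 (taken as two-sided). The effective sample per arm is n_eff = n / [1 + (m − 1) × ICC]. The detectable difference d solves d = 2.80 × √{[p1(1 − p1) + p2(1 − p2)] / n_eff}, where p2 = p1 + d.

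- Mothers, 10%, ICC 0.15: n_eff = 1200/1.75 = 685.7; d = 4.99 points.
- Mothers, 50%, ICC 0.30: n_eff = 1200/2.50 = 480; d = 8.97 points.
- AWWs (2 per village), 10%, ICC 0.25: n_eff = 400/1.25 = 320; d = 7.6 points.
- AWWs, 40%, ICC 0.45: n_eff = 400/1.45 = 275.9; d = 11.8 points.

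These match the stated 5–9 and 8–12. The ICC cannot be a district ICC: with 1200/3 = 400 mothers per district, values of 0.15 to 0.30 would give design effects of 1 + 399 × ICC, about 61 to 121.

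**2. Adding a district term.** Let ρ be the share of total variance due to districts that remains within matched pairs after baseline adjustment. With three districts per arm,

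Var(difference) = 2p(1 − p) × [DEFF/1200 + ρ/3].

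The second term contains neither the number of villages nor the number of mothers.

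**3. Illustration at p = 0.30, village ICC 0.20** (DEFF = 2.0). The protocol gives no value for ρ, so the values below are assumptions. Village term: 0.42 × 2/1200 = 0.00070, SE 2.65 points. District term: 0.42 × ρ/3 = 0.14ρ. The 80% detectable difference at ρ = 0 is 2.80 × 2.65 = 7.4 points.

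| Assumed ρ | District SD, √(0.21ρ) | SE (points) | Type I error, village-level 5% test | Power at 7.4 points, correct SE |
|---|---|---|---|---|
| 0 | 0 | 2.65 | 5% | 80% |
| 0.002 | 2.0 | 3.13 | 10% | 66% |
| 0.005 | 3.2 | 3.74 | 17% | 51% |
| 0.01 | 4.6 | 4.58 | 26% | 37% |
| 0.02 | 6.5 | 5.92 | 38% | 24% |

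Type I error = 2[1 − Φ(1.96 × 2.65/SE)]; power = Φ(7.4/SE − 1.96). At ρ = 0.005, for example, SE = √(0.00070 + 0.00070) = 3.74 points.

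These use normal critical values; with few districts the loss is greater. A t-test on three district-pair differences (2 df) has only about 35% power at the stated detectable difference even when ρ = 0.

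**4. How far baseline adjustment helps.** The planned model was simulated for a continuous outcome: 201 village pairs in 3 district pairs, a baseline mean from 4 dyads per village, and village-level robust standard errors. Here ρ is the district share before adjustment, from 0.005 to 0.02.

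| District difference | Type I error, ICC 0.15 | Type I error, ICC 0.30 |
|---|---|---|
| Fully persistent from baseline | 10%–23% | 7%–13% |
| Fully time-varying | 22%–45% | 26%–49% |

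With no district variance, type I error was close to 5%. Adjustment is partial because the baseline village mean is noisy: its coefficient was about 0.4 to 0.64, not 1.

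**The case against.** Much of the case on the other side stands.

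- **The design deals with part of the district variation.** A reader might infer that power fails under any district variation at all. The protocol does not support that. Neighbouring districts are paired within a division, and the pair effects absorb what they share. The baseline village mean is included expressly to control stable confounders at village level and above, and it partly does so. Only what remains within pairs matters.
- **The size is assumed.** A reader might take 17% or 38% as this study's actual error rate. No district ICC is given, so the direction is established and the size is not.
- **The standard errors are not specified.** The Analysis plan does not say how they are computed, and an analysis plan not at hand may settle it. The error-rate statement therefore concerns village-level inference, which the power section implies. The power statement is in print and stays conditional either way.
- **The limits of the design are partly disclosed.** The article calls the design less robust than a randomised one and concedes that confounding may remain. It presents this as bias, and does not link the small number of districts to power or standard errors.
- **A strict district-level test would be a poor replacement.** A sign-flip test over three pairs cannot give p below 2/2³ = 0.25. Over six pairs the minimum is 2/2⁶ = 0.031, reached only if all six effects agree in sign. Because assignment was not random, such a test rests on an assumed symmetry. As the sole basis for claims it would also displace the state-specific objective.

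The power calculation also takes no credit for pairing or baseline adjustment, which may lower the village-level variance. That does not shrink the district term.

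**Conclusion.** The concern holds in a conditional form. The stated 80% power per state, for mothers and for AWWs, is correct arithmetic for villages as independent clusters. It holds only if there is no residual district variation within matched district pairs after baseline adjustment, and the same condition applies to the 5% level of any village-level test. Pair effects and the baseline mean narrow the gap. Neither removes district-specific change between baseline and endline, and larger samples within the same districts cannot reduce it.

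Under the assumed range of 0.002 to 0.02, power falls to between about 66% and 24% and type I error rises to between about 10% and 38%. Those figures rest on 30% prevalence, village ICC 0.20, three districts per arm and normal critical values. This does not show that the design is invalid or that its results will be false positives. It shows that the protocol states a property without the condition on which it depends.

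**What to change.** 1. In the power section, state that the 5–9 and 8–12 point figures are conditional on no residual district variation within matched district pairs, and give the sensitivity range alongside, labelled as assumed.
2. For each primary outcome, report the six district-pair effects, three per state.
3. Add a pooled analysis at district-pair level, for example a t-test on 5 df across the six pairs, as a sensitivity analysis. Do not make a six-pair sign-flip test the sole basis for claims of effectiveness.
4. Describe state-specific p-values as conditional on the sampled districts.

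The cost is a change of wording and a small additional analysis, with no new data. The price is that the stated power and the state-level claims become less favourable.
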